## Abstract

**Background:**

There is scanty data in India on polycystic ovary syndrome (PCOS) from several small, undersized, convenience-based studies employing differing diagnostic criteria and reporting varied regional prevalence. It is difficult to draw clear-cut conclusions from these studies; therefore, the present multicentric, well-designed, large-scale representative countrywide epidemiological study on PCOS across India was conceived with the aim to generate the actual prevalence rates of PCOS in India with a total sample size of approximately 9000 individuals.

**Objective:**

The primary objectives of the study are to estimate the national prevalence of PCOS in India and the burden of comorbidities and to compare the variation in efficacy of standard therapeutic modalities for metabolic dysfunction in women with PCOS.

**Methods:**

This multicentric umbrella study consists of three different substudies. Substudy 1 will involve recruitment of women aged 18-40 years using a multistage sampling technique from randomly selected polling booths across urban and rural areas to estimate national prevalence, phenotypic variation, and risk factors among regions. Substudy 2 involves recruitment of subjects from the community pool of substudy 1 and the institutional pool for quantitation of comorbidities among women with PCOS. Substudy 3, an interventional part of the study, aims for comparison of variation in efficacies of common treatment modalities and will be conducted only at 2 centers. The eligible consenting women will be randomized in a 1:1 ratio into 2 arms through a blinding procedure. All these women will undergo clinical, biochemical, and hormonal assessment at baseline and at 3 and 6 months. The data generated will be analyzed using the reliable statistical software SPSS (version 26).

**Results:**

The study is ongoing and is likely to be completed by April 2022. The data will be compiled and analyzed, and the results of the study will be disseminated through publications.

**Conclusions:**

The Indian Council of Medical Research–PCOS study is the first of its kind attempting to provide accurate and comprehensive data on prevalence of PCOS in India.

**Trial Registration:**

Clinical Trials Registry–India CTRI/2018/11/016252; ctri.nic.in/Clinicaltrials/pmaindet2.php?trialid=26366

**International Registered Report Identifier (IRRID):**

DERR1-10.2196/23437

## Plain English Summary

Polycystic ovary syndrome (PCOS) is a multifactorial disorder with unknown etiology and numerous clinical manifestations in reproductive-aged women around the world. The metabolic abnormalities linked to this syndrome include type 2 diabetes, insulin resistance (IR) obesity, abnormal glucose tolerance (AGT), and cardiovascular diseases (CVD). The sketchy data and escalating prevalence of PCOS and associated comorbidities among Indian women led to organization of a multidisciplinary brainstorming meeting held September 11, 2014, at Indian Council of Medical Research (ICMR) headquarters, and the ensuing recommendations suggested formulation of the ICMR–PCOS Task Force to conduct a multicentric, multiphase study among Indian women with PCOS.

This is a multicentric, multispecialty study with a common comprehensive predesigned protocol involving 10 centers located in the 6 zones of the country. The women from the community (rural and urban) will be screened using a validated screening questionnaire, after obtaining a written informed consent from the subjects. The proforma will capture all details about menstrual cyclicity, acne, hirsutism, socioeconomic status, family history of PCOS, etc. The national prevalence will be calculated from the community pool for substudy 1. All biochemical and hormonal analysis will be done by standard assays using similar kits, reagents, and equipment. Ultrasonography (US) including magnetic resonance imaging (MRI) of the abdomen will be performed using a common approved protocol. The various comorbidities such as AGT, nonalcoholic steatohepatitis, and sleep apnea will be evaluated from both the pools (ie, hospital cohort and community cohort in substudy 2). The interventional randomized double-blind trial (ie, oral contraceptive pills [OCPs] vs metformin) will be conducted at only 2 centers for substudy 3. Apart from this, a knowledge, attitude, and practices survey of service providers in the public health system will be conducted to understand the training needs and gaps in the health system addressing PCOS management.

## Introduction

### Overview

Polycystic ovary syndrome, affecting approximately 116 million women worldwide, is now considered the commonest endocrinopathy of reproductive-aged women [1,2]. Stein and Leventhal initially described it as the association of bilateral ovaries with amenorrhea in 1935 [3,4]. Now, its association with a constellation of metabolic aberrations including obesity, AGT, IR, non-alcoholic fatty liver disease (NAFLD), metabolic syndrome, sleep apnea, stroke, CVD, neuropsychiatric comorbidities, microalbuminuria, mitogenesis, etc, in addition to cosmetic and reproductive dysfunction, is increasingly being recognized [5-9].

Global prevalence of PCOS among geographical zones is reported differently as 5%-10% in developed countries, 5%-30% in the United States, and 3.7%-22.5% across India [10-13]. Since there is no specific established treatment protocol available, early diagnosis and management is likely to reduce the risk of long-term complications of PCOS. The etiology of the disorder is being actively investigated; various reports speculate on the environmental and genetic factor interactions responsible [14-16]. Various small, regional, poorly designed studies using varying diagnostic criteria suggest a high prevalence of PCOS in India, seemingly running parallel to the epidemic of noncommunicable diseases, especially type 2 diabetes. There are no systematic representative data on the prevalence of PCOS or burden of its comorbidities among Indian women to date [17-31]. The existing data hint at the potential for large-scale epidemiological studies on PCOS across India to generate the actual prevalence and picture of the disease in the community. Therefore, there is an immense need to generate nationwide data on the prevalence of PCOS, including its comorbidities, besides any variations in phenotypes or treatment responses among Indian women.

To address these issues concerning PCOS among Indian women, ICMR, New Delhi, has taken the initiative to conduct a nationwide multicentric study titled “Evaluation of prevalence, regional phenotypic variation, co-morbidities, risk factors and the variations in response to different therapeutic modalities among Indian women with polycystic ovary syndrome (PCOS): A Multicenter study across India” to quantitate the burden of PCOS and its comorbidities in its phase 1.

### Objectives

The objectives of the proposed study are as follows:

#### Primary Objectives

The primary objectives are to (1) estimate national prevalence, phenotypic variations, and risk factors of PCOS in the community; (2) estimate the burden of comorbidities such as metabolic syndrome, dyslipidemia, cardiovascular complications, NAFLD, psychiatric abnormalities, sleep apnea, AGT including type 2 diabetes, and impairment of quality of life (QOL) among known cases of PCOS; and (3) compare the variation in efficacy of standard therapeutic modalities for metabolic dysfunction in women with PCOS (2 sites, All India Institute of Medical Sciences [AIIMS] and Sher-i-Kashmir Institute of Medical Sciences [SKIMS]).

#### Secondary Objectives

The secondary objective is to assess knowledge and management practices among service providers in the public health sector on PCOS to develop a standard screening and training modules to facilitate management of PCOS at different levels of the public health care system.

## Methodological Steps and Study Design

### Overview

The milestone steps to proceed with estimation of national prevalence, phenotypic variation, and risk factors involve a community-based, cross-sectional survey to recruit women belonging to the age group of 18-40 years from both rural (n=500) and urban areas (n=500) across 6 zones (ie, North, South, East, West, North East, Central India). ICMR has always been a leader in developing ethical standards for any human research considering the moral, ethical, and social values and ethos of diverse populations in the country. The proposed study will be conducted according to the Helsinki Declaration of 1975 and stands approved by the Institutional Ethics Committees at all 10 study sites. A written informed consent will be obtained from the participants assuring their understanding of the purpose of the study and obligations and consequences of their participation.

### Detailed Methodology: Substudies 1 and 2

#### Participant Selection

Women aged 18-40 years who are not pregnant or lactating and have been residing in the area for 1 year or more will be included in the study. Women who are known to have PCOS will be recorded for the purposes of PCOS prevalence and will only be evaluated in detail for substudy 2 if they are drug-naïve. Women taking oral contraceptives, steroids, antiepileptics, or other drugs known to interfere in glucose or lipid metabolism will not be evaluated in detail and will be excluded from the study.

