#### Inclusion Criteria

The following are the criteria for inclusion: women aged 18-40 years who are permanent residents of the area (>1 year), willing to participate in the study and sign informed consent, known to have PCOS, and not on treatment.

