#### Exclusion Criteria

Pregnant or lactating women and those with cognitive limitations, physical limitations, or both that prevented them from answering the questionnaire will be excluded from the study.

Women with a history of drug intake such as steroids, androgens, oral contraceptives, antiepileptics, or drugs known to interfere in glucose or lipid metabolism will also be excluded.

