### Evaluation Methods

Both the subgroups of women coming from the community pool and institutional pool will be evaluated as per the defined protocol for clinical, biochemical, and hormonal assessment during the second to the seventh day of the cycle. In the institutional pool, women attending endocrinology, gynecology, dermatology, or other related clinics for symptoms and signs of PCOS will be asked to report to the research staff or PCOS station for detailed evaluation as per the common protocol. Support will be obtained from the public health system for enrolling women from the community and conducting further examinations, investigations, and follow-up at their facilities in urban and rural areas. All those women who are drug-naïve will undergo clinical assessment (anthropometry, hirsutism scoring, acne, oligomenorrhea, androgenic alopecia, primary infertility), biochemical evaluation (liver function test, kidney function test, lipids, oral glucose tolerance test [OGTT]), high-sensitivity C-reactive protein (hsCRP) and cytokine tests (selected cases), 25-hydroxyvitamin D [25OHD] testing (selected cases), and hormonal estimations (thyroxine [T_4_], thyrotropin, luteinizing hormone [LH], follicle-stimulating hormone [FSH], prolactin [PRL], cortisol, anti-Müllerian hormone [AMH], dehydroepiandrosterone sulfate [DHEAS], 17-hydroxyprogesterone [17OHP], sex hormone–binding globulin [SHBG], serum total testosterone and insulin at 0, 30, and 120 minutes, estradiol [E2], progesterone [P4], procollagen type I N-terminal propeptide, CrossLaps, anti–thyroid peroxidase, ferritin, B_12_, pro–brain natriuretic peptide, and C-peptide levels). The blood samples will be transported in a cold chain to one center (SKIMS, Srinagar) for lab analysis using electrochemiluminescence immunoassay (ECLIA; Roche Diagnostics USA). Analytes such as SHBG and serum total testosterone levels will be transported to one center (SKIMS, Srinagar) for purposes of uniformity and will be analyzed in one go. In a subset of cases (n=100), total testosterone and SHBG will be assayed by ECLIA and liquid chromatography–tandem mass spectrometry in the Department of Endocrinology, AIIMS, New Delhi.

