The 1990 National Institutes of Health (NIH) consensus conference criteria will be taken as the qualifying criteria. This necessitates the presence of the following 2 criteria: (1) oligoovulation or anovulation (intermenstrual interval ≥35 days, presence of ≤8 cycles per year, or both) and (2) clinical signs, biochemical evidence, or both of hyperandrogenism after ruling out disorders with similar clinical presentation such as hyperprolactinemia, Cushing syndrome, congenital adrenal hyperplasia, and androgen-secreting tumors with specific laboratory analysis (cortisol, 17OHP, and DHEAS). To compare, the 2003 Rotterdam criteria and the 2009 Androgen Excess and PCOS (AE-PCOS) Society criteria will also be employed. Therefore, US examination to satisfy the diagnosis of PCOS by these criteria will be done. A common standard operating procedure for abdominal examination (liver, pancreas, ovary, and uterus) will be adhered to with a built-in system to minimize interobserver and equipment variations. The 2003 Rotterdam criteria necessitate the presence of 2 of the following 3 criteria: (1) oligoovulation, anovulation, or both; (2) clinical signs, biochemical evidence, or both of hyperandrogenism; and (3) polycystic ovary in US. The 2009 AE-PCOS Society criteria necessitate the presence of the following criteria: (1) oligoovulation and/or anovulation (intermenstrual interval ≥35 days, presence of ≤8 cycles per year, or both) and/or polycystic ovary in US and (2) clinical signs, biochemical evidence, or both of hyperandrogenism. To exclude etiologies that could mimic PCOS like Cushing syndrome, late-onset adrenal hyperplasia, or androgen-producing neoplasm, we will exclude thyroid disorders, renal hyperplasia, hyperprolactinemia, and late-onset congenital adrenal hyperplasia by medical history and hormone tests. This will further serve to unravel various comorbidities such as AGT, metabolic syndrome, IR, cardiovascular risk, psychiatric morbidities, and impairment of QOL (Figure 3). Besides, these women will be evaluated for risk factors such as birth weight, parental history of gestational diabetes or PCOS, risk of low birth weight, precocious pubarche, prepubertal obesity, antiepileptic drug intake, familial association with lifestyle diseases, etc. Abdominal MRI for comparing ovarian morphology will also be done at a selected center (SKIMS, Srinagar) using the predesigned uniform protocol.

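### The eligibility sections conflict on whether a known, previously treated PCOS case enters the prevalence count, and no check of her diagnosis against the study's case definition is stated

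*Protocol article*

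**What the plan says.** All references are to the protocol article.

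- **Participant Selection, counting rule,** on women with an existing diagnosis: "known to have PCOS will be recorded for the purposes of PCOS prevalence and will only be evaluated in detail for substudy 2". The sentence makes that evaluation conditional on being drug-naïve.
- **Participant Selection, next sentence,** on current users of several named drug classes and of "other drugs known to interfere in glucose or lipid metabolism will not be evaluated in detail and will be excluded from the study".
- **Inclusion Criteria (substudy 1):** a woman with an existing diagnosis is admitted if she is "known to have PCOS, and not on treatment".
- **Exclusion Criteria (substudy 1):** the list removes "Women with a history of drug intake such as steroids, androgens, oral contraceptives, antiepileptics, or drugs known to interfere in glucose or lipid metabolism".
- **Evaluation Methods, work-up:** "All those women who are drug-naïve will undergo clinical assessment", followed by the biochemical and hormonal tests.
- **Evaluation Methods, case definition:** "The 1990 National Institutes of Health (NIH) consensus conference criteria will be taken as the qualifying criteria". This requires ovulatory dysfunction plus hyperandrogenism, with similar disorders ruled out by cortisol, 17OHP and DHEAS. The Rotterdam and AE-PCOS criteria are applied for comparison.

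The article does not define drug-naïve, and it states no other check of an earlier diagnosis, such as medical records or the criteria originally used.

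**The concern.** National prevalence is part of the first primary objective. The counting rule separates being recorded for prevalence from being evaluated. If every recorded woman were also worked up, the drug-naïve condition would have no effect. A diagnosis made elsewhere can therefore enter the count without the results that the study's own definition requires. As Evaluation Methods sets out the criteria, ovulatory dysfunction plus polycystic ovaries on ultrasound satisfies Rotterdam but not NIH, so a prior diagnosis made on that basis would not qualify under NIH. Such a woman also has no criterion-specific status for the planned three-way comparison. The Abstract justifies the study partly by the differing diagnostic criteria of earlier work, and this route would bring that problem back.

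Other sentences exclude many of the same women. Two centres could each follow the text and handle the same woman differently: one records her as a case, the other passes to the next name on the electoral roll.

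**Working it through.** **Step 1. Apply the rules to four women who already carry a PCOS diagnosis.**

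| Woman | Counting rule (Participant Selection) | Next sentence, same section | Inclusion Criteria | Exclusion Criteria | Work-up |
|---|---|---|---|---|---|
| Never treated | recorded | not affected | admitted | not affected | yes |
| Now on a listed drug, e.g. an oral contraceptive | recorded | excluded | not admitted | excluded | no |
| Past use of a listed drug, now off treatment | recorded | not affected (covers current use) | admitted | excluded if history means lifetime use | no, if drug-naïve means never treated |
| Past use of an unlisted drug only, now off treatment | recorded | not affected | admitted | not affected, unless the open-ended list is stretched | no, if drug-naïve means never treated |

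Only the first row is settled. The second contradicts itself. The third depends on two undefined terms. Only the fourth gives a woman who is counted unverified without meeting an exclusion, and even that needs the strict reading of drug-naïve.

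**Step 2. Reproduce the planned precision.** Estimation of Sample Size for Substudy 1 gives 10% prevalence, a ±1 point margin, 20% nonresponse and a design effect of 2.

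- With z rounded to 2: n = 4 × 0.10 × 0.90 / 0.01² = 3600; 3600 / 0.8 = 4500; 4500 × 2 = 9000. This matches the plan.
- With z = 1.96 the total is about 8643, so the stated 9000 is slightly conservative.
- Effective responders: 9000 × 0.8 / 2 = 3600, giving a half-width of 1.96 × √(0.09 / 3600) = 0.98 points.

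The sample size is not in dispute. It supplies the yardstick of about 1 point.

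**Step 3. Illustrate the bias in each direction.** Let f be the share of sampled women with a prior diagnosis who are not evaluated, and v the share of those who truly meet NIH. Neither is in the documents. I assume f = 0.5% to 2% and v = 50% to 80% (so 20% to 50% fail NIH), with true NIH prevalence 10%.

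- All counted: 0.10 + f(1 − v)
- All excluded from numerator and denominator: (0.10 − fv) / (1 − f)

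| f (women of 9000) | v | All counted | Bias | All excluded | Bias | Gap |
|---|---|---|---|---|---|---|
| 0.5% (45) | 80% | 10.10% | +0.10 | 9.65% | −0.35 | 0.45 |
| 0.5% (45) | 50% | 10.25% | +0.25 | 9.80% | −0.20 | 0.45 |
| 1% (90) | 80% | 10.20% | +0.20 | 9.29% | −0.71 | 0.91 |
| 1% (90) | 50% | 10.50% | +0.50 | 9.60% | −0.40 | 0.90 |
| 2% (180) | 80% | 10.40% | +0.40 | 8.57% | −1.43 | 1.83 |
| 2% (180) | 50% | 11.00% | +1.00 | 9.18% | −0.82 | 1.82 |

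Wrongly counted women range from 9 (9000 × 0.005 × 0.20) to 90 (9000 × 0.02 × 0.50). The upward bias reaches 1 point only when both assumptions sit at their extremes; the middle values (1%, 35% failing) give 0.35 points. The gap between the two readings passes 1 point once f is slightly above 1%.

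Two simplifications apply. If the history exclusion is read as lifetime use, past users move from the counted column to the excluded column, so the upward figures shrink. The excluded column removes only women with a prior diagnosis; excluding unaffected drug users as well would shrink the denominator further and partly offset the downward bias.

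**The case against.** A reader might infer that the plan definitely counts unverified cases and so overstates NIH prevalence. The documents do not support that, for four reasons.

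- The Exclusion Criteria refer to a history of drug intake. On a lifetime reading, a woman who once took an oral contraceptive or a glucose-modifying drug is out of substudy 1, and prevalence would fall rather than rise.
- Being recorded for prevalence is not the same as entering the NIH numerator, still less all three numerators. That is the natural reading, but the text does not say it.
- If drug-naïve simply means currently untreated, every admitted known case is evaluated and no admitted woman goes unverified.
- The Participant Selection limit concerns evaluation for substudy 2, and the questionnaire section invites all screen-positive women for detailed assessment with no exception for prior diagnoses. Only the drug-naïve wording in Evaluation Methods restricts the work-up more generally.

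These points stand, and they remove any claim about direction. They do not remove the conflict, because each settles it by choosing one section over another. If the exclusions prevail, the counting rule has almost nothing left to act on. If the counting rule prevails, the exclusions are not applied as written.

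It can also be said that tabulating unverified diagnoses belongs in an analysis plan that is not shown. That is fair for the detail of the analysis. It does not cover eligibility and case-counting statements that the article itself makes and that disagree.

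**Conclusion.** The point holds as an inconsistency in who counts as a case for the first primary objective, with no stated verification of a prior diagnosis against NIH. Neither the sign nor the size of the bias can be fixed from the documents. On assumed inputs (0.5% to 2% of women affected, 20% to 50% of them failing NIH, true prevalence 10%), it runs from +0.1 to +1.0 points if all are counted and from −0.2 to −1.4 points if all are excluded. The upper part of each range is comparable to the planned ±1 point margin; the lower part is minor. The plan should be corrected, but this does not invalidate the survey or its sample size.

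**What to change.** 1. Reconcile Participant Selection, Inclusion Criteria, Exclusion Criteria and Evaluation Methods on whether known cases who are not drug-naïve enter the prevalence numerator and denominator. Define drug-naïve, and say whether the history exclusion means current or lifetime use.
2. State that a prior diagnosis alone does not make a woman a case in the NIH, Rotterdam or AE-PCOS estimates, and that their confirmed numerators use evaluated women.
3. Record the number of women with a prior diagnosis who are not evaluated, including those excluded for drug use. Under Sampling Design an ineligible woman is replaced by the next on the list, so these women must be logged before replacement.
4. Report bounds for each estimate, with none and with all of these women counted.
5. Report previously diagnosed PCOS as a separate, self-reported figure.

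Estimating the status of unevaluated women from drug-naïve known cases is at most an optional sensitivity analysis, since confirmation rates may not carry over to treated women.

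The cost is wording, one tally and a small extra analysis, with no new visits or assays. Where recruitment is already under way, the tally depends on what the field eligibility records kept. The downside is a wider and slightly less favourable reported range for prevalence.
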